### Settings and Participants

To be able to provide precise estimates of mean and variance that will aid in the planning of a larger and sufficiently powered efficacy trial, a reasonable rule of thumb for continuous variables (eg, pain intensity) is a sample size of 12 per group [78]. Based on previous experience with this population and intervention, we could expect an attrition rate of 20%. However, an attrition rate of 30% could be anticipated in the long term at the 6-month follow-up [43]. Hence, we will recruit 32 participants—16 (50%) per group. Patients will be selected according to the following criteria: (1) age ≥18 years, (2) first-time elective coronary artery bypass grafting and valve replacement via a median sternotomy, (3) worst pain in the past week score ≥4/10 [79], (4) ability to understand and complete questionnaires in English, and (5) ability to use an electronic device such as a smartphone, computer, or tablet. Patients will not be eligible for the study if they (1) had undergone a previous thoracotomy or mastectomy and (2) were unable to consent because of physical or cognitive incapacity.

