Regarding the preliminary effects of the intervention, the protocol will favor an intention-to-treat approach for the analysis of results, thus involving all patients who were randomly assigned. Participants’ flow will be reported according to the Consolidated Standards of Reporting Trials guidelines for psychological interventions [109]. The statistical analysis will be mostly descriptive (mean and SD for continuous outcomes and frequency and proportion for categorical outcomes) with 95% CIs when appropriate. Pain intensity, pain interference, opioid use, mindfulness, pain acceptance, pain-related catastrophic thoughts, and depression or anxiety scores will be summarized using descriptive statistics presented per group at each time point. Furthermore, treatment effects will be estimated and presented with 95% CIs at each time point. Between-group differences will be assessed by fitting linear mixed models for each outcome: pain intensity, pain interference, opioid use, mindfulness, pain acceptance, pain-related catastrophic thoughts, and anxiety or depression. Outcome variables will be regressed on the intervention group (EG vs ACG) and time (preintervention, postintervention, and 3 and 6 months after surgery) after covarying baseline values to perform statistical matching on prerandomized values, thus ensuring that comparisons by treatment group are independent of baseline differences [110]. Of primary interest is the impact of the intervention on the prevalence and severity of CPSP (ie, pain intensity, pain interference, and opioid use) at 3 and 6 months. However, these analyses will be undertaken primarily for illustrative purposes, as the study is not powered to show statistical significance. An α level of significance of .05 will be used for all analyses.

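### Sixteen per group leaves about 11, not 12, at 6 months under the protocol's own 30% attrition; the sample-size justification should be restated

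*Protocol article*

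**What the plan says.** The whole sample-size justification is in the protocol article, Settings and Participants. Its purpose is given as "To be able to provide precise estimates of mean and variance that will aid in the planning of a larger and sufficiently powered efficacy trial". The target follows: "a reasonable rule of thumb for continuous variables (eg, pain intensity) is a sample size of 12 per group". Two attrition rates come next. From previous experience the authors state that "we could expect an attrition rate of 20" per cent, and then that "an attrition rate of 30% could be anticipated in the long term at the 6-month follow-up". The next sentence opens with *Hence* and concludes that "we will recruit 32 participants", 16 in each group.

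The Statistical Analysis section bears on the weight of the 6-month visit. It says: "Of primary interest is the impact of the intervention on the prevalence and severity of CPSP", and names 3 and 6 months as the time points. It also promises treatment-effect estimates with 95% confidence intervals at each time point. The same paragraph describes these analyses as illustrative and says that the study lacks power for significance tests.

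**The concern.** The justification is a short chain: a target of 12 per group, a loss of 20% and then of 30% at 6 months, and so 16 per group. The conclusion comes directly after the 30% rate, so a reader takes 16 as the number that protects 12 per group at 6 months. It does not.

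What is at stake is whether the plan describes correctly what its sample will deliver. A reader who plans the later trial from the 6-month data would expect at least 12 per group there and estimates described as precise. On the protocol's own figures the expected number is about 11, and no expected interval width is given from which to judge the precision.

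**Working it through.** **Inputs from the protocol article.** Target of 12 per group; attrition of 20% in general and 30% at 6 months; 32 recruited, 16 per group (all Settings and Participants). Allocation is 1:1 in blocks of 4 (Study Design). Intervals are 95% (Statistical Analysis). No SD is given, so precision is shown in SD units.

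**Step 1: reproduce the stated 16 per group.** The number to recruit is n/(1 - d), where n is the target and d the proportion lost.

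- d = 0.20: 12/0.80 = 15 per group, 30 in total.
- d = 0.25: 12/0.75 = 16 per group, 32 in total. The protocol does not state this rate.
- d = 0.30: 12/0.70 = 17.1, rounded up to 18 per group, 36 in total (nine complete blocks of 4).

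Neither stated rate gives exactly 16 by this formula. Multiplying instead, 12 x 1.30 = 15.6, does round up to 16.

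**Step 2: number retained from 16 per group.**

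- At 20% loss: 16 x 0.80 = 12.8. Target met.
- At 30% loss: 16 x 0.70 = 11.2. Target missed by 0.8 per group.
- Largest loss that still leaves 12: 1 - 12/16 = 25%.

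**Step 3: chance of keeping at least 12.** This assumes that participants drop out independently and at the same rate in both groups. At 30% loss, P(Bin(16, 0.70) >= 12) = 0.45 in one group and 0.45 squared = 0.20 in both. At 20% loss the figures are 0.80 and 0.64.

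**Step 4: what the lost participant costs in precision.** The unadjusted 95% half-width for a between-group difference, in SD units, is t(0.975, 2n - 2) x sqrt(2/n). The 95% limits for the pooled SD, as multiples of the estimate, are sqrt(df/chi-square quantile) with df = 2n - 2.

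| Completers per group | Half-width of difference | Pooled-SD limits |
|---|---|---|
| 11 | 0.89 SD | 0.77 to 1.44 |
| 12 | 0.85 SD | 0.77 to 1.42 |
| 13 | 0.81 SD | 0.78 to 1.39 |

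For an assumed SD of 1.5 to 3 points on the 0-10 pain scale, the half-width with 11 per group is about 1.3 to 2.7 points. With 12 per group it is about 1.3 to 2.5 points.

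**The case against.** The best defence is that nothing depends on the gap. It is less than one participant per group at one of four time points, and the table shows that no planning decision would change between 11 and 12. This stands, and it is why the point is minor.

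The text also never says that 12 must remain at 6 months; 12 is a rule of thumb for a sample size. That is true. But citing a 6-month attrition rate and then drawing the recruitment figure from it has no other evident purpose, so the inference is fair.

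The analysis is planned as linear mixed models with baseline as a covariate. The unadjusted completers-only half-width is therefore somewhat pessimistic. With an assumed baseline correlation of 0.3 to 0.6, multiplying 0.89 by sqrt(1 - r squared) gives about 0.85 to 0.71 SD. This also stands, and the restated figure should be labelled unadjusted.

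A reader might go further and infer that the pilot fails a precision requirement, or that the slip will leave the later trial underpowered. The documents support neither. The protocol sets no numerical precision target, so there is none to miss. The risk in planning from a point estimate of the SD comes with any small pilot and would be nearly the same with 12 per group. The protocol itself calls the effect analyses illustrative. Nor does the match with 12 x 1.30 prove how 16 was obtained; it is only one possible explanation.

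**Conclusion.** The stated sample size does not follow from its last premise. With 16 per group and 30% loss, about 11 per group are expected at 6 months, against a target of 12; meeting the target at that rate would take 18 per group. At 20% loss the target is met. The error is certain as arithmetic and minor in consequence: about one participant per group, at one of the two time points of primary interest, and 0.04 SD in the half-width of a difference.

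The retained numbers use only the protocol's figures, with 12 read as the number to be retained. The probabilities assume independent and equal dropout, and the interval widths assume an unadjusted comparison of completers with a common SD. That the word *precise* needs qualifying is a judgement from the width of these intervals, not a breach of a stated criterion.

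**What to change.** Restate the justification in Settings and Participants along these lines:

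> Thirty-two participants give about 13 per group if 20% are lost and about 11 per group at 6 months if 30% are lost, slightly below the 12-per-group rule of thumb. With 11 per group, the unadjusted 95% CI half-width for a between-group difference is about 0.9 SD, and the 95% CI for the pooled SD runs from about 0.77 to 1.44 times the estimate.

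Let the second sentence replace the unqualified word *precise*. Recruiting more patients is not required: going to 36 would restore the arithmetic (18 x 0.70 = 12.6) but leave the intervals about as wide, and the Results section already reports slow recruitment. No rule for sizing the later trial needs to be fixed in this protocol.

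The cost is two sentences of text. Design, recruitment and analysis are unchanged; the stated expectations become slightly less favourable.

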### Procedures

All participants will complete baseline measures via a telephone interview (with responses entered in a Qualtrics survey) at the time of enrollment (T0). Figure 2 depicts participant flow during the study protocol.

**Figure 2 figure2:**
[figure not shown]
Participant flow diagram. MBCT: mindfulness-based cognitive therapy.

### Choice of Comparators

Most MBI studies include the usual care control groups. A meta-analysis conducted by the Agency for Health Care Research and Quality including 18,753 articles found that only 47 (3%) trials included an active control treatment [80]. This approach only contributes to showing the absolute benefit of an MBI and fails to demonstrate if that MBI has more value than clinical attention alone. Based on our previous findings, accounting for therapeutic contact with clinicians is important in this phase [38]. Moreover, guidance from clinicians embedded in web-based interventions has an impact on outcomes [81]. Hence, attention control is relevant in highlighting the benefits of MBI. Moreover, ACGs may help mitigate the lack of oversight on usual care by standardizing the information received by people in the control groups [82]. Finally, although it is admitted that double blinding is complex to implement in studies with psychosocial interventions, ACGs may contribute to blinding to a certain extent [82]. Thus, an attention control approach is used in this study. Although the web-based standardized session needs to be credible and includes a video recording from a clinician, it was carefully developed so that it does not include any active ingredient [82,83].

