### Study Design

A double-blinded pilot RCT will be used to assess the brief web-based MBCT intervention in the 6 months following cardiac surgery (coronary artery bypass grafting and valve replacement). This study received ethical approval from the institutional review board of Florida State University in January 2021. An experienced research assistant (RA) will be responsible for participants’ recruitment and informed consent procedures at the time of follow-up with the surgeon (usually 2-4 weeks after surgery). The study will be advertised in the surgeon’s offices and surgical units with posters and flyers. Social media platforms and newspapers will also be used. If interested, potential participants will contact the RA via telephone or email, and the inclusion criteria will be assessed. After baseline measures have been collected, participants will be randomized into two groups by the principal investigator (PI): one receiving both the brief 4-week web-based MBCT intervention and the usual care procedure (experimental group [EG]); the second group receiving only one standardized educational web-based session in the first week along with weekly reminders for 3 weeks and the usual care procedure (attention control group [ACG]). At the end of the intervention, participants will be asked if they received the intervention to evaluate their blinding. Participants from the ACG will be given the opportunity to receive the entire intervention once the study is complete.

Computer software will generate the randomization schedule: permuted block randomization with block sizes of 4 and an allocation ratio of 1:1. The randomization list and opaque sealed envelopes numbered sequentially will be prepared by the PI’s colleague who will not be involved in this study. The RA who will be responsible for the entire data collection will be blinded to the patient group assignment. Participants in both groups will receive gift cards of US $25 at each of the four data collection time points (baseline, after intervention, 3 months after surgery, and 6 months after surgery) for a total of US $100.

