### Treatment Conditions

Usual care includes a booklet with brief instructions on postoperative care and surveillance of complications provided during hospitalization, and a general assessment and some instructions regarding medication intake and safe return to activities as needed at the time of the follow-up appointment. In addition to usual follow-up care, in the first week of enrollment, the ACG will have access to a 15-minute standardized educational web-based session on persistent postsurgical pain, how pain and stress may interact, and their potential impact on recovery. Brief instructions on self-care (eg, selecting activities that bring a sense of pleasure or mastery) and helpful self-statements (eg, “I will overcome this pain” and “this pain will not last”) will also be provided. In addition, three weekly reminders will be sent to encourage participants to review the web-based session.

Patients assigned to the EG will receive a brief web-based MBCT intervention adapted from the brief four-session clinical manual on MBCT for chronic pain by day [84]. Four 15- to 30-minute sessions are planned (Textbox 1). Each session is structured as follows: an introductory video of the clinician, mindfulness exercise audio recording, wrap-up and weekly homework, or maintenance instructions from the clinician.

Outline of the four brief mindfulness-based cognitive therapy sessions.

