**Sessions’ Main Themes and Mindfulness Strategies**
Session 1: persistent postoperative painBody scan (20 minutes)Session 2: stepping out of automatic thoughtsMindful breathing (10 minutes)3-minute breathing spaceSession 3: acceptance and self-care activitiesMindful breathing (10 minutes)Session 4: wrap-up and maintenance plan3-minute breathing spaceBody scan (20 minutes)

The first session will first focus on providing feedback regarding persistent postsurgical pain, the role played by the brain in pain perception, and the relationships between thoughts, feelings, and behaviors. It will end with teaching one mindfulness strategy, that is, body scan, or bringing detailed awareness to each body part and bodily sensation, which is considered an accessible introductory exercise to mindfulness meditation [47]. The second session will focus on pain-related automatic thoughts and teaching the second mindfulness strategy, that is, mindful breathing or focusing attention on breathing—the inhale and the exhale. Moreover, a brief portable 3-minute breathing space strategy will also be presented. The third session will focus on acceptance and self-care strategies and practicing mindful breathing. The fourth session consists of providing feedback and reminders about cognitive reactions to pain and suggesting a maintenance plan along with an opportunity to practice the strategies. The participants will be asked to practice guided meditation (audio recording) 5 days a week for a total of 4 weeks: beginning with body scan in week 1, mindful breathing and the 3-minute breathing space in week 2, and participants may choose either practice for weeks 3 and 4. Participants will also receive a booklet with information about persistent postsurgical pain, an overview of the 4-week program, and a description of the strategies. Participants in the EG will receive reminders as needed, that is, if they do not view the weekly session at all.

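### The control session is said to hold no active ingredient, yet it shares pain education and self-care content with MBCT, so the contrast is not MBCT over attention alone

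*Protocol article*

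**What the plan says.** Choice of Comparators argues that a usual-care control shows only the absolute benefit of a mindfulness intervention and cannot separate it from the effect of clinical contact. The trial therefore uses an attention control. The session has to be credible and features a clinician on video, but "it was carefully developed so that it does not include any active ingredient".

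Treatment Conditions describes what controls receive: a "15-minute standardized educational web-based session on persistent postsurgical pain, how pain and stress may interact, and their potential impact on recovery". They also receive "Brief instructions on self-care (eg, selecting activities that bring a sense of pleasure or mastery) and helpful self-statements", with two example statements, one about overcoming the pain and one about the pain being temporary. After the first week, "three weekly reminders will be sent to encourage participants to review the web-based session".

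The outline of the experimental sessions has session 1 "providing feedback regarding persistent postsurgical pain, the role played by the brain in pain perception, and the relationships between thoughts, feelings, and behaviors". It continues: "The second session will focus on pain-related automatic thoughts and teaching the second mindfulness strategy". Then: "The third session will focus on acceptance and self-care strategies and practicing mindful breathing".

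Theoretical Framework names pain acceptance and pain-related catastrophic thoughts as the two variables that the intervention targets.

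**The concern.** The protocol gives the comparator a property, inertness, and then describes content that lacks it. The property matters because the choice of comparator rests on it. If the control session carried only attention and credibility, a difference between the arms could be read as the value of MBCT beyond attention. If it also carries pain education, self-care planning and coping statements, the same difference answers another question: what MBCT adds to that content.

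Two misreadings follow if the claim stays.

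- A small or null difference could be reported as no MBCT effect beyond attention, although both arms had received education and coping content.
- The estimates could be carried into a larger trial with a usual-care or inert comparator, where they would not apply. Settings and Participants says that the pilot's estimates are meant to help plan such a trial.

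**Working it through.** This point rests on text. The only design figure, 32 participants, comes from a rule of thumb of 12 per group raised for attrition (at 20%, 12 / 0.80 = 15 per group; the plan takes 16). It uses no effect size and does not depend on what the control session contains.

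**Step 1: set the content side by side.**

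| Control session (Treatment Conditions) | MBCT sessions (session outline) | Overlap |
|---|---|---|
| Education on persistent postsurgical pain and on pain and stress | Session 1: persistent postsurgical pain; thoughts, feelings and behaviours | Same topic, named in both arms |
| Choosing self-care activities | Session 3: acceptance and self-care | Self-care named in both arms; acceptance in MBCT only |
| Coping self-statements | Session 2: pain-related automatic thoughts | Same target, different technique |
| None | Body scan, mindful breathing, 3-minute breathing space, home practice | MBCT only |

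Two of the three control components match MBCT content by name. The third shares a target only.

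**Step 2: compare the amounts.** Controls have one 15-minute session, plus three reminders to look at it again. The experimental group has four sessions of 15 to 30 minutes, so 4 × 15 = 60 to 4 × 30 = 120 minutes, which is 4 to 8 times the control time. It is also asked to practise on 5 days a week for 4 weeks, or 20 days. The arms are clearly different, and the shared content is a small part of the programme by time.

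**Step 3: ask whether the protocol itself treats such content as inert.** It does not. The Background describes MBCT as mindfulness strategies combined with cognitive therapy, so cognitive content is part of the tested package. It reports that the team's earlier brief, web-based, cognitive behavioural intervention may shift psychological risk factors and reduce pain interference. It also argues that teaching psychological self-management strategies is likely to improve coping.

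**Step 4: relate the content to the outcomes.** The self-statements bear on pain-related thoughts, which the Pain Catastrophizing Scale measures. Self-care activity selection bears on continuing with daily activities, and activity engagement regardless of pain is one of the two subscales of the acceptance questionnaire. The control content therefore touches the domain of both mechanism outcomes. Whether it changes the scores is not known.

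**Step 5: look for a size.** The document gives no effect size for MBCT, none for the control session and no share common to the two. No magnitude can be computed.

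**The case against.** The strongest reply is that shared content defines a comparison and does not bias it. A credible control needs some relevant material. Pain education serves the protocol's stated aims of standardising what controls are told and supporting blinding. This stands: a comparator with education and coping content is legitimate. It does not rescue the claim that the content is inert.

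A second reply is that an active ingredient here means one specific to mindfulness. On that reading the claim would be true, since the body scan, breathing exercises and home practice are in one arm only. But the sentence excludes any active ingredient, and the package under test includes cognitive therapy. The two references cited for the claim are not at hand, so a narrower intended meaning can be neither confirmed nor excluded. The text should state it.

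Third, the overlap can be overstated. Session 2 is about stepping back from automatic thoughts, which is not the same as being handed self-statements. The evidence in the Background concerns a targeted intervention during hospitalisation, not this session. Both points stand.

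Fourth, Statistical Analysis calls the effect analyses mainly illustrative and unpowered. This stands and limits the harm. It does not settle what the estimates are estimates of.

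A reader might also draw on Study Design, which says: "Participants from the ACG will be given the opportunity to receive the entire intervention once the study is complete". That could suggest that controls have already had part of the intervention. The ordinary meaning is the full four-session programme, and the point does not rely on it.

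**Conclusion.** The point holds as a contradiction within the protocol with a consequence for interpretation. The control session does not have the property claimed for it. The between-group difference estimates MBCT over brief pain education and coping content. What clearly sets the experimental group apart is the mindfulness practice, the homework and the larger dose, together with teaching, such as that on acceptance, that the control description does not name.

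The size and direction of any effect of the shared content are unknown. Three stronger readings are tempting, and the document supports none of them:

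- **That the MBCT effect is diluted by a calculable fraction, so that a later trial would be too large by a known factor.** No passage supplies the fraction. If the later trial keeps this comparator, the observed difference is the right planning quantity. The error arises only if the comparator changes.
- **That statements about overcoming pain lower acceptance in controls and exaggerate the MBCT gain.** This is conceivable, but nothing in the document shows it.
- **That the contrast is biased toward the null on every outcome.** This would require the control content to act in the same direction as MBCT throughout, which is not established.

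The conclusion assumes only that the session is delivered as described. It changes what the trial may claim about MBCT against attention alone; it does not invalidate the pilot.

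**What to change.** Reconcile Choice of Comparators with Treatment Conditions through wording:

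1. Delete the claim of no active ingredient, or limit it to no mindfulness-specific ingredient.
2. Label the arm a brief pain-education and coping comparator.
3. State in Statistical Analysis that the effect estimates, especially for catastrophizing and acceptance, describe MBCT over that content. A null result is then not evidence of no MBCT effect beyond attention.
4. State that planning figures taken from the pilot apply to a trial with the same comparator and should not be carried to one with an inert or usual-care control.

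The cost is a few sentences and a less favourable claim about the comparator. The session itself need not be changed. Recruitment began in June 2021, and replacing content now could split the planned 16 controls between two comparators and might weaken the credibility and blinding that the attention control was chosen to provide.
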